## Expedited reporting procedure

According to the Roche standard, in this noninterventional study all individual cases documented as an adverse event are reported to the sponsor within 24 h (page 1 "Contact") if they fulfil the following criteria:

- serious adverse event, defined as an event which
  - is fatal or life-threatening or
  - requires hospitalization or prolongation of hospitalization or
  - results in persistent or significant disability / incapacity or
  - is a congenital anomaly / birth defect or
  - is an important medical event (*)
- (*) An important medical event is an event that may not be fatal, not life-threatening or do not require hospitalization but which may considerably impair the patient. Adverse events are also medically important if they require an intervention / treatment to prevent their occurrence which corresponds to those in the definition "serious adverse event".

The following events are reported independent of possible documentation of an adverse event in the expedited procedure:

- product quality / technical complaints
- reports involving suspect counterfeit or counterfeit drugs / falsified medicinal products
- occupational exposure (e.g. needle-stick injury in medical personnel)

Please use the enclosed bilingual AE Report Form "Adverse Event Form" for this purpose (see Annex 14.2). or alternatively the contact form at the following link:

**https://www.roche.de/service/kontakt.php**

## Pregnancies

In accordance with the Roche standard, the occurrence of pregnancies (pregnancy / lactation, paternal exposure) is recorded in the case record form during the noninterventional study and for up to 7 months after the end of the therapy phase in partners of patients and for up to 4 months in female patients after the end of the therapy phase and is additionally to be reported by the physician to Roche within 24 h using the record form provided for this purpose: "German Local Drug Safety Bilingual RO-GNE: Pregnancy Record Form (English/German)" (see Annex 14.3).

Pregnancies (pregnancy / lactation, paternal exposure) are also to be reported in the case of adverse events / adverse drug reactions. The physician is requested to advise the patient regarding the risks associated with continuing the pregnancy including the possible effects on the fetus. Pregnancies are to be followed up accordingly.

Pregnancies of the partners of affected persons are also to be documented and reported to the sponsor if an influence on the course of pregnancy cannot be ruled out because of the pharmacological behaviour of the medicinal product. Pregnant partners of affected patients should be advised in a similar manner as described above. Pregnancies are to be followed up accordingly.

# Statistical aspects

## Number of patients

Overall, it is planned to document at least 9000 patients in specialized practices and outpatient departments with experience in treating patients with interferon and ribavirin over a recruitment period of at least four years.

Since about 16,000 patients currently receive interferon therapy in outpatient departments and specialized practices in Germany every year, this results in a sample size of about 12.5 %. A representative sample can be assumed because of the chosen distribution mode within the Association of German Resident Gastroenterologists and other centres experienced in interferon treatment.

## Choice of centres

Physicians throughout the Federal Republic of German familiar with interferon therapy can participate.

## Analysis plan

The descriptive statistical evaluation is performed by the company factum GmbH.

All recorded data – depending on the type of characteristics – are presented descriptively as mean, standard deviation, minimum, maximum, median, 1st and 3rd quartile or their frequency distribution. Categorical characteristics are presented with absolute and relative frequencies within the individual categories.

For continuous variables multiply recorded over time, basic statistics with absolute differences between the end of observation and the baseline value are calculated.

For the tolerability analysis, adverse drug reactions are counted by frequencies using the respective preferred terms categorized according to organ systems. These survey tables are additionally stratified according to the clinical relevance of the drug effect as "serious/non-serious".

Moreover, an assessment of the clinical tolerability of the hepatitis C therapy is performed by the physician.

For the safety laboratory analysis, basic statistics over time are generated per parameter. Additionally, the frequencies of changes in categorical laboratory values (classified into "normal", "increased", "reduced") are presented per laboratory parameter between the baseline value and end of treatment and between the end of treatment and follow-up.

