| Selected patient population: | Therapy data from patients over 18 years of age, with a diagnosed chronic hepatitis C with detectable virus replication and no contraindication for the use of peg (40kDa)-interferon alfa-2a (Pegasys®) or combination therapy with ribavirin (Copegus®), can be documented (please see product information).  Women of childbearing potential should use adequate contraception. It is important that female patients of childbearing potential and their sexual partners use 2 contraceptive methods at the same time during treatment and 4 months after treatment discontinuation. During this time pregnancy tests have to be performed monthly.  Particular attention is also required and pregnancy should be avoided 7 months after treatment discontinuation in female sexual partners of male patients taking ribavirin (Copegus®). Both should use adequate contraception.  Ribavirin (Copegus®) must not be used in pregnant women.  Please see the current German product information. |
| Planned number of patients: | 9000 |
| Selected physician population: | Participation is open to all physicians familiar with interferon therapy in Germany. |
| Planned number of centers: | 600 |
| Selection criteria: | Selection will take place by a specialized field force. Criteria are experience of physicians in the treatment of chronic hepatitis C and a known excellent documentation quality in the past |
| Main parameters of interest: | Demographic data, anamnesis of hepatitis C, viral genotype and viral load, relevant laboratory parameters, histology (if available), concomitant diseases, data of treatment and dosage of Peginterferon alfa-2a and ribavirin and other concomitant medication, virological outcome: RVR, EVR, EOT, SVR, (severe) adverse events |
| Procedures: | Baseline, routine visits at weeks 2, 4, 8, 12, 24, 36, 48, EOT and EoFU, additional modules for HIV-coinfection, opioid substitution, cardiovascular risk, HCV after liver transplantation, and pharmacoeconomics |

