| Duration: | According to the product information, the duration of the combination therapy with ribavirin (Copegus®) for chronic hepatitis C depends on the virus genotype. Naive patients with virus genotype 1 and genotypes 2/3 should be treated for 48 weeks and 24 weeks, respectively. Patients with low viral load at baseline (< 800,000 IU/ml) and Rapid Viral Response (HCV-RNA undetectable after 4 weeks of treatment), can sufficiently be treated for 24 weeks only, in case of genotype 1, and for 16 weeks only, in case of genotypes 2/3.  This recommendation is identical for patients with genotype 4.  Duration of retreatment in patients who have failed prior therapy should be 48 weeks in general. In case of genotype 1 patients with prior non-response, retreatment duration of 72 weeks is recommended.  The recommended duration of Pegasys monotherapy is 48 weeks.  In clinical studies with peg­interferon alfa-2a (Pegasys®) alone or in combination with ribavirin (Copegus®) (see product information), a Rapid Viral Response was defined by a HCV RNA load below the limit of detection after 4 weeks of therapy whereas an early virological response was defined by a HCV RNA load below the limit of detection or by a reduction of the virus titre by 99 % of the initial value after 12 weeks of therapy.  Of patients with genotype 1 or 4 and no early virological response after 12 weeks therapy with peg­interferon alfa-2a (Pegasys®) alone or in combination with ribavirin (Copegus®), only a very small number (<2%) achieved sustained virological response.  In those patients, therapy should be discontinued, taking into account the low probability of a sustained virological response.  In patients with genotype 2 or 3, early virological response is known to be very high (97 %) and subsequently a high SVR rate is achieved after 24 weeks. Therefore, viral load determination after 12 weeks of treatment is not deemed to be necessary.  Planned FPI: 01/01/2008  Planned LPI: 31/12/2011  Planned LPO: 30/06/2013 |

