### Hepatitis C

Chronic virus hepatitis C is a disease which often takes a clinically insidious course and threatens the affected patients mainly because of its late complications (liver cirrhosis, hepatocellular cancer). In June 2002, peg­interferon alfa-2a (Pegasys®) was approved for the treatment of chronic virus hepatitis C by the European Agency for the Evaluation of Medicinal Products (EMEA) on the basis of two international marketing authorization studies (Zeuzem et al. 2000, Heathcote et al. 2000).

In patients with chronic hepatitis C, Pegasys® is best used in combination with ribavirin.

Since January 2003, ribavirin Copegus® has been approved by the Federal Institute for Drugs and Medical Devices (BfArM) in Germany for combination with peg­interferon alfa-2a (Pegasys®) in the treatment of chronic hepatitis C.

The combination of Pegasys® and ribavirin is indicated in non-pretreated patients and in patients who have failed to respond to previous treatment with interferon alfa (pegylated or non-pegylated) alone or in combination therapy with ribavirin.

Monotherapy with peg­interferon alfa-2a is indicated mainly when there is intolerance or contraindications to ribavirin.

Pegylated interferon alfa-2a (Pegasys®) is administered to patients with genotype 1 and the more rarely occurring genotypes 4, 5 and 6 in the combination with ribavirin initially for 12 weeks. The decision whether to prolong the therapy by 36 weeks to altogether 48 weeks or to discontinue the treatment is based on an HCV-RNA assay: either the virus assay in week 12 is negative (equivalent to a reduction in the viral load below the limit of detection) or a reduction was achieved in the original serum HCV-RNA by 2 log steps (equivalent to 99 % of the baseline value before start of treatment).

Patients who did not show this defined "early virological response" (EVR) after 12 weeks will with very high probability (97 %) also not have any lasting therapeutic success after further treatment (Ferenci P et al. 2001, Fried MW et al. 2001). This procedure saves the patient unnecessary stress from treatment side effects and saves costs.

In patients with genotypes 2 or 3, on the other hand, such a high EVR of 97 % is achieved that no monitoring of the viral load after 12 weeks is recommended.

As regards the duration of treatment, a further multicentre international study for patients with genotypes 1 and 4 also confirmed a treatment duration of 48 weeks (Hadziyannis SJ et al. 2004).

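### Absolute change from baseline is a poor scale for HCV-RNA: in IU/ml it largely reflects baseline load once the fall reaches about 1 log (minor)

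*Protocol*

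**What the plan says.** Protocol Section 8.3 (Analysis plan) gives one rule for change over time in continuous variables: "basic statistics with absolute differences between the end of observation and the baseline value are calculated". It names no variable, unit or transformation, and makes no exception. Of categorical data it says: "Categorical characteristics are presented with absolute and relative frequencies within the individual categories".

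Quantitative HCV-PCR is a repeated continuous variable. Section 7.2.2 lists it at baseline, allows it at weeks 4, 8, 12, 24 and 48, and lists it again at end of treatment and at follow-up week 24. Viral-load thresholds are given in IU/ml (Synopsis, Duration; Section 4.1.3).

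Response is defined relatively. Besides undetectability, the Synopsis defines early virological response by "a reduction of the virus titre by 99 % of the initial value after 12 weeks of therapy", and Section 4.1.3 expresses the same criterion as "a reduction was achieved in the original serum HCV-RNA by 2 log steps". The Synopsis lists as main parameters "virological outcome: RVR, EVR, EOT, SVR, (severe) adverse events".

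**The concern.** A difference in IU/ml and a relative fall measure different things. A patient who starts very high and falls by less than 99% can show a far larger drop in IU/ml than a patient who starts low and clears the virus. A table built this way would then describe the baseline distribution more than the effect of treatment.

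This matters for group comparisons. Section 4.2 plans to set specialised practices against hospital outpatient departments, and the study data against clinical studies. If baseline load differs between the groups compared, the raw-change table can favour the higher-load group whatever its response.

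**Working it through.** **The protocol's own figure.** Relative fall = 1 - 10^(-d) for a fall of d log10. With d = 2 this is 1 - 0.01 = 0.99, so the stated equivalence of 2 log steps and 99% is correct.

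**One baseline.** Absolute change = -baseline × (1 - 10^(-d)). Take 800,000 IU/ml, the protocol's own cut-off, as an example baseline:

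| End of observation | Load (IU/ml) | Absolute change | log10 change |
|---|---|---|---|
| unchanged | 800,000 | 0 | 0 |
| 0.5-log fall | 252,982 | -547,018 | -0.5 |
| 1-log fall | 80,000 | -720,000 | -1.0 |
| 1.5-log fall | 25,298 | -774,702 | -1.5 |
| 1.9-log fall (titre criterion missed) | 10,071 | -789,929 | -1.9 |
| 2-log fall (criterion met) | 8,000 | -792,000 | -2.0 |
| undetectable | about 0 | about -800,000 | about -4.5 if set to 25 |

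From 1 log to 1.9 log, a patient who misses the titre criterion shows 90% to 98.7% of a cleared patient's absolute change.

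**Different baselines.** A fall from 10,000,000 to 200,000 IU/ml is 98%, short of the criterion, and gives -9.8 million. A fall from 400,000 to undetectable gives -0.4 million. The ratio is 9.8/0.4 = 24.5 in favour of the patient who missed the criterion.

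**Separation across patients.** Assumptions not in the documents:
- log10 baseline is normal with mean 5.9 and SD 0.5, 0.8 or 1.0, the same in both groups;
- cleared patients are set to 25 IU/ml;
- the log fall in non-responders has SD 0.3 (0.2 for the 1.5-log case);
- 100,000 simulated patients per group.

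The table gives the probability that a random cleared patient shows the larger fall than a random non-responder (0.5 means no separation), as a range over the three SDs:

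| Mean fall in non-responders | IU/ml scale | log10 scale |
|---|---|---|
| none, or back to baseline | 0.82 to 0.87 | 1.000 |
| 0.5 log | 0.58 to 0.64 | 1.000 |
| 1 log | 0.52 to 0.53 | 1.000 |
| 1.5 log | 0.50 to 0.51 | 0.999 to 1.000 |

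The rank correlation of absolute change with baseline is -1.00 in cleared patients. In non-responders it is -0.99 to -1.00 for falls of 1 log or more, -0.83 to -0.88 at 0.5 log, and about 0 when the load is unchanged.

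**Unequal baselines.** Suppose non-responders with a 1.5-log fall start 0.4 log higher than cleared patients (log10 means 6.1 and 5.7). The mean difference in log10 of the absolute fall is 0.4 + log10(0.968) = 0.386. The probability that the non-responder shows the larger raw fall is Φ(0.386 / (SD × √2)): 0.71 for SD 0.5, 0.63 for SD 0.8, and 0.61 for SD 1.0.

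**The case against.** The strongest reply is that Section 8.3 does not fix the scale. A difference of log10 values is also an absolute difference, and the analysis plan, which is not shown, may specify one. That stands as a limit on the point. Still, the protocol states viral load in IU/ml, mentions logs only in the response criterion, and exempts no variable, so a plain reading gives a difference in IU/ml.

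A reader might infer that the change merely mirrors baseline and cannot tell any non-responder from a cleared patient. The documents and the arithmetic do not support that. With unchanged or relapsed load the change is about 0, against a median of about -790,000 in cleared patients, and separation is 0.82 to 0.87.

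A reader might also infer that the main efficacy result is compromised. It is not. Response is judged by RVR, EVR, end-of-treatment response and SVR, and categorical results are reported as frequencies.

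Quantitative PCR is also optional late in the study. Section 7.2.2 recommends only the qualitative test at follow-up, and likewise at week 24 for genotypes 2/3 and week 48 for genotypes 1/4. The table may therefore be sparse. Partial falls can still enter it: Section 6.2 allows final documentation at end of treatment if that comes sooner, and quantitative PCR can be recorded there.

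Section 8.3 also lists medians and quartiles, which protects against a few extreme values but not against the wrong scale. With the same baseline distribution in both groups, the median change after a uniform 1.5-log fall is 96.8% of the median after clearance. Section 7.3 says baseline values are taken into account but does not say how.

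**Conclusion.** The point holds as a minor correction. Read in IU/ml, the Section 8.3 rule gives an HCV-RNA change that is driven largely by baseline load in cleared patients and in partial responders with falls of about 1 log or more. It hardly separates those two groups (0.50 to 0.53, against 0.999 or more on the log10 scale) and can favour groups with higher baseline load.

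The single-baseline figures are exact arithmetic. The separation figures rest on assumed baseline distributions and sizes of fall, and they depend strongly on the size of fall. The effect is confined to a descriptive change table and does not reach the virological response rates.

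**What to change.** In Section 8.3, state that HCV-RNA is summarised as the log10 value and the log10 change from baseline, with a stated convention for results below the limit of detection and the proportion below detection shown alongside. Apply the same rule to HIV-RNA and HBV-DNA where they are quantified; the same arithmetic applies, although no figures were worked for them here. Keep absolute differences for the other continuous variables.

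The cost is a short addition to the text and a transformation in the tables. No new data are needed. The one choice to make is the value assigned to undetectable results, which affects the size of the mean log10 change and so must be stated.

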The following information on the dosage of ribavirin (Copegus®) in combination with peg­interferon alfa-2a (Pegasys®) can also be derived from the study of Hadziyannis et al.:

Patients with genotype 1 with a body weight of less than 75 kg should receive 1000 mg ribavirin (Copegus®) orally per day, and with a body weight above 75 kg should receive 1200 mg. This recommendation has so far also applied to the interferon-ribavirin combination treatment of patients with genotype 2 or 3. The current data now show that patients with genotype 2 or 3 require only 800 mg ribavirin (Copegus®) orally per day regardless of body weight if administered in combination with peg­interferon alfa-2a (Pegasys®). This change in the recommendation for the ribavirin dosage on combination with peg­interferon alfa-2a (Pegasys®) can reduce unnecessary stress from treatment side effects and can also lower costs.

Further international studies have demonstrated the high efficacy and good safety profile of peg­interferon alfa-2a (Pegasys®) in combination with ribavirin (Copegus®) in patients with normal GPT (Zeuzem et al. 2004) and in HIV/HCV coinfected patients (Torriani et al. 2004).

These findings have meanwhile been incorporated in numerous national guidelines, including the German guidelines, as well as recommendations of international associations for liver research (EASL, AASLD).

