#### Examination after 2 weeks

- Laboratory parameters
  GPT (=ALT), GOT (= AST), GGT
  Other laboratory parameters:
  hemoglobin, platelets, WBC, neutrophils (%), bilirubin
- Adverse events (including suspected cases) with substance-specific causality survey
- Date and dosage information for peg­interferon alfa-2a (Pegasys®): 180 µg and ribavirin, e.g. Copegus® (including dose changes and rationale for change, dose schedule)
- Concomitant medication
- New comorbidities
- Clinical symptoms: none, fatigue, fever, muscular stiffness, skin changes, hair loss, joint pain, muscle pain, abdominal pain, nausea, reflux, weight loss, headache, insomnia, irritability, restlessness, depression, depressive mood, psychosis, impaired concentration, anorexia, jaundice, pruritus, elevated GPT, craving / withdrawal-like symptoms, other;
  causal relationship with Pegasys and/or ribavirin
- Treatment-related sick leave (duration) since the last examination
- Pregnancy test

#### Examinations during treatment in week 4, 8, 12, 24, 36 and 48

- *Only in week 12, 24, 36 and 48:* body weight
- Laboratory parameters
  GPT (=ALT), GOT (= AST), GGT,
  Other laboratory parameters:
  hemoglobin, platelets, WBC, neutrophils (%), bilirubin, creatinine
  *Only in week 12, 24, 36 and 48*: TSH, blood glucose (fasting), HbA1c*Only in week 24:* ANA, LKM, SMA, AMA, SLA, Trak, MAK, rheumatoid factors
- Hepatitis laboratory diagnostic tests
  HCV-PCR (quantitative/qualitative), *in week 4 and 12 recommended*
  HCV-PCR (qualitative), *only in week 24* for GT-2/3, o*nly in week 48 for GT-1/4 recommended*
  (HCV-PCR (quantitative/qualitative) can be documented in week 4, 8, 12, 24 and 48)
- Adverse events (including suspected cases) with substance-specific causality survey
- Date and dosage information for peg­interferon alfa-2a (Pegasys®): 180 µg and ribavirin, e.g. Copegus®: (including dose changes and rationale for the change, dose schedule)
- Concomitant medication
- New comorbidities
- Clinical symptoms: none, fatigue, fever, muscular stiffness, skin changes, hair loss, joint pain, muscle pain, abdominal pain, nausea, reflux, weight loss, headache, insomnia, irritability, restlessness, depression, depressive mood, psychosis, impaired concentration, anorexia, jaundice, pruritus, elevated GPT, craving / withdrawal-like symptoms, other;
  causal relationship with Pegasys and/or ribavirin
- Treatment-related sick leave (duration) since the last examination
- (Monthly) pregnancy test

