#### At the end of treatment / documentation (end of therapy):

- Therapeutic consequence: reason for end / discontinuation of therapy
- Reasons for therapy discontinuation: lacking virological response, lacking tolerability, lacking compliance, unplanned event (e.g. imprisonment, detoxification), patient's wish, patient no longer attended, other reason
- Concomitant medication
- New comorbidities
- Body weight
- Hepatitis C laboratory diagnostic tests
  HCV-PCR (quantitative/qualitative), *only recommended in week 12*
  HCV-PCR (qualitative), *only recommended in week 24 for GT-2/3, only in week 48 for GT-1/4*
  (HCV-PCR (quantitative/qualitative) can be documented in week 4, 8, 12, 24 and 48)
- Hepatitis B laboratory diagnostic tests (only if chronic hepatitis B was documented at the baseline examination): HBsAg (+/-), HBeAg +/-; HBV-DNA quant./qual., anti-HBs (+/-); anti-HDV (+/-), HDV-RNA (+/-, qual. or quant.)
- Autoantibodies: ANA, LKM, SMA, AMA, SLA, Trak, MAK, rheumatoid factors, other
- Laboratory parameters
  GPT (=ALT), GOT (= AST), GGT,
  Other laboratory parameters:
  hemoglobin, platelets, WBC, neutrophils (%), bilirubin, creatinine, TSH, blood glucose (fasting), HbA1c, triglycerides, cholesterol, HDL, LDL, serum ferritin
- Clinical symptoms: none, fatigue, fever, muscular stiffness, skin changes, hair loss, joint pain, muscle pain, abdominal pain, nausea, reflux, weight loss, headache, insomnia, irritability, restlessness, depression, depressive mood, psychosis, impaired concentration, anorexia, jaundice, pruritus, elevated GPT, craving / withdrawal-like symptoms, other;
  causal relationship with Pegasys and/or ribavirin
- Treatment-related sick leave (duration) since the last examination
- (Monthly) pregnancy test
- Adverse events (including suspected cases) with substance-specific causality survey
- Clinical assessment of the tolerability of Pegasys and the combination with ribavirin (Copegus®): very good, good, moderate, poor
- Quality of life assessment compared to before treatment: symptom-free; improved, but not symptom-free; unchanged
- Alcohol consumption no/yes, if yes, inquiry ≤/ > 40 g/d and drinks/d in the last 30 days
- Compliance (assessed by the physician):
   very good: all medications taken
   good: max. 10% not taken
   satisfactory: max. 20% not taken
   poor: > 20% not taken
- Quality of life assessment compared to before treatment: symptom-free; improved, but not symptom-free; unchanged

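### Laboratory statistics over time have no stratum or fixed cohort, so the on-treatment values at weeks 36 and 48 come from a selected subset and do not continue the earlier curve

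*Protocol*

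**What the plan says.** Section 8.3, Analysis plan, on laboratory safety: "For the safety laboratory analysis, basic statistics over time are generated per parameter". No subgroup, denominator or common cohort is given. For adverse drug reactions the same section does name a split, serious against non-serious.

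The laboratory values come from the main module (7.2.2), under the heading "Examinations during treatment in week 4, 8, 12, 24, 36 and 48". Week 2, end of treatment and follow-up week 24 are separate records.

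Course length is described in the Synopsis (Duration):
- "Naive patients with virus genotype 1 and genotypes 2/3 should be treated for 48 weeks and 24 weeks, respectively".
- With low baseline viral load and rapid response, patients "can sufficiently be treated for 24 weeks only, in case of genotype 1, and for 16 weeks only, in case of genotypes 2/3".
- Retreatment generally lasts 48 weeks, or 72 weeks for genotype 1 patients with prior non-response.
- On genotype 1 or 4 without early response at week 12: "In those patients, therapy should be discontinued, taking into account the low probability of a sustained virological response".

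The end-of-treatment form lists "Reasons for therapy discontinuation: lacking virological response, lacking tolerability, lacking compliance", among other reasons.

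Section 8.3 also plans two analyses tied to each patient's own course. One is the difference between the end of observation and baseline for repeated continuous variables. The other is categorical laboratory shifts from baseline to end of treatment and from end of treatment to follow-up.

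**The concern.** A table or curve of haemoglobin, neutrophils or platelets by visit invites the reader to follow it from left to right as one group's experience on treatment. Here the group changes along the way. Patients on 16- and 24-week courses have gone to their end-of-treatment record before week 36, and so have those who stopped for non-response or intolerance.

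Two distortions are possible. If short-course patients have milder laboratory changes, their departure can look like late worsening. If patients with the poorest values stop early, their departure can look like recovery. Neither needs any patient's value to change.

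Safety is part of the main objective, and the protocol plans a descriptive comparison with existing safety and approval data. A pooled time course could feed that comparison.

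**Working it through.** The plan gives no figure for this point, so there is none to reproduce. The check has two parts.

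**1. Who can contribute on treatment at each visit (protocol text only)**

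| Planned course | Weeks 2 to 12 | Week 24 | Week 36 | Week 48 |
|---|---|---|---|---|
| 16 weeks | yes | no | no | no |
| 24 weeks | yes | yes (end) | no | no |
| 48 weeks | yes | yes | yes | yes (end) |
| 72 weeks | yes | yes | yes | yes |

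Early stoppers leave each row sooner. The patients at weeks 36 and 48 are thus a subset of those seen earlier, selected by genotype, viral load, response, prior treatment and tolerability.

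**2. How far a visit mean can move with no within-patient change (illustration)**

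Assumptions, none of them in the documents:
- s = share on courses of 24 weeks or less, 20% to 50%.
- d = share of long-course patients who stop before week 36, 10% to 30%.
- D = long-course completers minus short-course patients, in SD.
- E = long-course completers minus long-course stoppers, in SD.
- Everyone still contributes at week 24. This ignores 16-week courses and earlier stops.

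Share still contributing at week 36 = (1 - s)(1 - d):
- s = 20%, d = 10%: 0.80 × 0.90 = 72%, or 6480 of 9000.
- s = 50%, d = 30%: 0.50 × 0.70 = 35%, or 3150 of 9000.

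Shift in the visit mean from week 24 to week 36 = D - (1 - s)[(1 - d)D + d(D - E)] = sD + (1 - s)dE. At s = 50%, d = 30%:
- D = E = 0: 0.
- D = 0.5, E = 0.5: 0.25 + 0.075 = +0.325 SD.
- D = -0.5, E = 0.5: -0.25 + 0.075 = -0.175 SD.
- D = -0.5, E = 0: -0.25 SD.

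With D from -0.5 to 0.5 and E from 0 to 0.5, the range is -0.25 to +0.33 SD.

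**The same two mechanisms for haemoglobin (assumed values)**
- Composition: shift = (1 - p)(d1 - d2), where p is the share on long courses and d1 and d2 are the falls in the long- and short-course groups. With p = 0.7, d1 = 3.0 and d2 = 2.5: 0.3 × 0.5 = 0.15 g/dl. With p = 0.5 and d2 = 2.2: 0.5 × 0.8 = 0.40 g/dl. This is an apparent extra fall.
- Selective stopping: simulation of 400,000 patients, baseline N(14.5, 1.4), fall N(3, 1.5) floored at 0, logistic stopping with slope -0.6 per g/dl. The share below 10 g/dl goes from 23.3% to 17.5% with 15% stopping and to about 12% with 34% stopping. The mean rises by about 0.31 and 0.66 g/dl. This is an apparent recovery.

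The two run in opposite directions and can partly cancel, so the net effect has no predictable sign.

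**The case against.** The strongest reply is that strata, denominators and fixed-cohort displays are commonly left to the statistical analysis plan, which is not shown. The sentence in 8.3 does not say that all patients are pooled or that tables are by visit; that is the natural reading, not the text. This stands in part: the absence of table detail is not itself an error, and if a later plan already splits these tables nothing more is needed. But 8.3 does specify a stratum where it wants one, and the display it describes is hard to interpret as written.

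A second reply is that the same section has safeguards. The end-of-observation differences and the shift tables are within-patient, concluding documentation is required even after discontinuation (6.1), and the report must present the effect of interfering variables (section 9). This also stands: those analyses do not depend on being treated at week 36 or 48. They do not give a time course, however, and a low value at week 8 that recovers by end of treatment does not appear in them.

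Three stronger readings are tempting, and the documents do not support them:
- *The late curve reflects who remains and not the drug.* Late values mix both, and the artefact is zero if the groups do not differ or the effects cancel.
- *Early and late visits describe different patients.* The late patients are a subset of the early ones.
- *The late group is simply the group with the higher ribavirin dose.* Section 4.1.3 says that "patients with genotype 2 or 3 require only 800 mg ribavirin (Copegus®) orally per day regardless of body weight" and describes weight-based dosing for genotype 1; it does not mention genotype 4 there. Patients at weeks 36 and 48 also include retreated patients, HIV-coinfected patients of any genotype and patients on 48-week monotherapy. Section 4.3 leaves the dose to the physician.

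**Conclusion.** The point holds as a matter of interpretation. By the protocol's own course lengths and stopping reasons, on-treatment laboratory values at weeks 36 and 48 come from a selected subset, and a pooled time course beyond about week 16 to 24 confounds within-patient change with change in composition. That much rests on the protocol text alone.

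The size does not. The 35% to 72% still contributing, the range in SD and the haemoglobin figures all rest on assumed course mixes, stopping rates and group differences. They show that the artefact could matter in either direction, not that it will. Nothing here invalidates the planned within-patient analyses. The point is a cheap improvement.

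**What to change.** - Present the laboratory statistics over time by genotype group, for example 1/4 and 2/3, with n on treatment at each visit. Genotype is already recorded at baseline. Intended course length is not among the listed baseline variables, so it is not a ready alternative.
- For weeks 36 and 48, also show the earlier visits in the same patients, those still on treatment at that visit. Late values are then compared within a fixed cohort. This is needed besides the genotype split because course length also varies within genotype. Change from baseline in whoever is present at each visit would not be enough, because the mean change also shifts as the group changes.
- Add the worst on-treatment value up to week 12 for all treated patients, including those who stop earlier. Twelve weeks lies within every planned course.
- State in the report that pooled week 36 and 48 values are not a continuation of the earlier curve.

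The cost is table programming and a longer set of tables. No new data and no change to patient procedures are needed. The fixed-cohort display describes only patients who stayed on treatment, and its title should say so.
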